### Statistical analysis

The proportion of independent walkers and the time to achieve independent walking will be compared between the two groups using the logrank test, in which those who do not achieve independent walking are censored at the time they are discharged. Survival analysis using Cox's regression will be used to compare the times in the two groups while allowing for possible confounding variables, such as other interventions received, and baseline sitting balance.

The five variables that reflect the quality of walking: speed, affected and intact step length, step width and cadence, will be compared between the two groups using Student's t-test, or Wilcoxon's rank-sum test for variables that are clearly not Normally distributed.

The four variables that reflect the mobility status: 6-min distance, number of falls since discharge, self-efficacy questionnaire about walking capability, and the Adelaide Activities Index will be compared between the two groups using Student's t-test, or Wilcoxon's rank-sum test for variables that are clearly not Normally distributed.

The two variables which reflect living arrangements: type of residence and the amount of support within the residence, will be analysed descriptively.

Descriptive data about lesion, neglect, spasticity and sensation will be used in post-hoc multiple regression analysis to examine if these factors affected walking outcome.

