### Randomization

Participants will be randomised into an experimental or a control group. We will stratify the randomisation. First, given the potential confounder of site, participants at each site will be randomised separately. Second, at each site, participants will be stratified according to initial level of motor disability since it has been found to affect outcome [16]. Since all the participants will be unable to walk on admission to the study, sitting balance will be used to stratify the allocation of participants to groups because it has been found to be a useful prognostic indicator of walking outcome [17-19]. Therefore, participants will be stratified according to Item 3 (Sitting Balance) of the Motor Assessment Scale for stroke [20] so that those with a score of 0–3 will be classified as severely disabled and those with a score of 4–6 will be classified as moderately disabled. Within each of the two strata (moderate versus severe level of disability), participants will be allocated randomly to one of two groups, the experimental group or the control group. Random permuted blocks will be used so that after every block (of 6–10 participants), the experimental and control groups will contain equal numbers. In summary, stratification will occur according to site (three sites) and level of disability (two levels). Therefore, there will be 6 strata and participants will be randomised separately within each stratum. The random sequence of group allocation will be concealed from the person recruiting participants.

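### Allocation is stratified by site and sitting balance, but the logrank test and the two-group tests are stated without strata, and site is not named as a covariate

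*Protocol article*

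**What the plan says.** **Design (Protocol article, Randomization).** Two factors define the allocation. For site: "given the potential confounder of site, participants at each site will be randomised separately". Sitting balance, split into a severe and a moderate level, is used because "it has been found to be a useful prognostic indicator of walking outcome". With three sites and two levels, "there will be 6 strata and participants will be randomised separately within each stratum". Balance inside each stratum is enforced by blocking: "Random permuted blocks will be used so that after every block (of 6–10 participants), the experimental and control groups will contain equal numbers".

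**Analysis (Protocol article, Statistical analysis).** The proportion of independent walkers and the time to walking "will be compared between the two groups using the logrank test"; no strata are mentioned. A Cox regression follows, "while allowing for possible confounding variables, such as other interventions received, and baseline sitting balance". Site is not in that list, but the list is given by example and so is open. The five gait variables and the four mobility variables "will be compared between the two groups using Student's t-test, or Wilcoxon's rank-sum test for variables that are clearly not Normally distributed", again with no strata or covariates. The section does not say whether the logrank test or the Cox model is the main comparison; the logrank test comes first.

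**The concern.** The design ties allocation to two factors, and most of the stated tests then ignore them. Balancing the arms within prognostic strata removes between-stratum variation from the treatment contrast. A test that ignores the strata still counts that variation as error. Its standard error is then too large, its true type I error falls below the nominal 5%, and some power goes unused. For time-to-event data there is a second effect: leaving out a strong prognostic factor pulls the marginal hazard ratio towards 1.

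What is at stake is efficiency, and agreement between design and analysis. The protocol's own reason for stratifying on sitting balance is that it predicts walking, which is exactly the condition under which the mismatch costs something.

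**Working it through.** **1. The plan's own figures reproduce and are not in dispute.** For 50% vs 75%, two-sided 0.05 and 80% power, the two-proportion formula gives 58 per group without and 66 with continuity correction (stated: 65). For 0.2 m/s with SD 0.27, 29 per group are needed (stated: 60 in total). Expected walkers with data are 130 × 0.8 × 0.8 = 83.2 (stated: 84), and 42 per group give 92.4% power (stated: over 90%).

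**2. Treatment effect on the hazard scale.** Under proportional hazards, 50% to 75% walking by six weeks means HR = ln(0.25)/ln(0.50) = 2.0.

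**3. Logrank test, plain vs stratified.** The stratified statistic is Z = Σ(O − E)/√ΣV, with O, E and V computed within each stratum and summed; the plain test treats everyone as one stratum. Simulation inputs from the protocol: N = 130, six strata, permuted blocks of 6 to 10, weekly testing, 50% of controls walking at six weeks. Assumed, because the protocol gives no figures: equal expected stratum sizes, discharge spread evenly over weeks 6 to 16, and the stratum effects below (rate of walking, moderate vs severe; highest vs lowest site). 3,000 runs per cell.

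| Sitting-balance ratio / site ratio | Type I error, plain vs 6-stratum | Power at HR 2, plain vs 6-stratum | Loss from plain test (points) |
|---|---|---|---|
| 1 / 1 | 0.058 vs 0.054 | 0.939 vs 0.921 | −1.9 (plain test better) |
| 2 / 1 | 0.039 vs 0.051 | 0.915 vs 0.930 | 1.5 |
| 2 / 1.5 | 0.032 vs 0.037 | 0.911 vs 0.927 | 1.6 |
| 3 / 1.5 | 0.026 vs 0.045 | 0.863 vs 0.917 | 5.4 |
| 4 / 2 | 0.021 vs 0.046 | 0.767 vs 0.907 | 14.0 |

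The simulation standard error is about √(0.9 × 0.1/3000) = 0.005 for power and √(0.05 × 0.95/3000) = 0.004 for type I error, so the rows with ratio 2 show a direction more than a precise size. These losses are at the design effect; at HR 1.7 the 3 / 1.5 row gives 0.611 vs 0.722.

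**4. What the planned Cox model recovers.** A second simulation (2,000 runs, discharge median 16 weeks, HR 2) gave this power:

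| Sitting-balance ratio / site ratio | Plain logrank | 6-stratum logrank | Cox with sitting balance | Cox with sitting balance and site |
|---|---|---|---|---|
| none | 93% | 90% | 93% | 93% |
| 3 / none | 84% | 89% | 92% | 92% |
| 3 / 1.5 | 84% | 90% | 92% | 93% |
| 4 / 2 | 76% | 88% | 88% | 90% |

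A third run (1,000 trials) gave, for plain logrank, 6-stratum logrank and Cox with sitting balance: 91%, 92% and 93% at a sitting-balance ratio of 2; 84%, 91% and 92% at 3 with site 1.5; 77%, 88% and 89% at 4 with site 2. The plain logrank test therefore loses 88 − 77 = 11 points in the last setting here, against 14 in step 3.

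**5. t-test on walking speed.** If strata explain a share R² of the variance and the arms are balanced within strata, the true standard error is √(1 − R²) times the one the plain t-test uses, so its type I error is about 2Φ(−1.96/√(1 − R²)): 0.039, 0.028 and 0.019 for R² = 0.1, 0.2 and 0.3. Simulation (N = 84, SD 0.27, 4,000 runs) gives slightly higher values because blocks are incomplete:

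| R² (assumed) | Type I error, plain vs adjusted | Power at 0.2 m/s, plain vs adjusted |
|---|---|---|
| 0 | 0.046 vs 0.046 | 0.915 vs 0.916 |
| 0.1 | 0.042 vs 0.055 | 0.929 vs 0.942 |
| 0.2 | 0.037 vs 0.055 | 0.939 vs 0.965 |
| 0.3 | 0.026 vs 0.055 | 0.946 vs 0.975 |

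The loss is 1.3, 2.6 and 2.9 points, near the ceiling of power; it would be larger for a smaller true difference.

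**The case against.** **The Cox model already does the work for time to walking.** This stands. In step 4 the Cox model with sitting balance equals or beats the six-stratum logrank test in every setting, and adding site gains at most about 2 points. A reader might infer that the power bought by stratification is simply wasted. The documents do not support that: the loss attaches to the logrank p-value, while the adjusted analysis of the same endpoint keeps most of the gain. One reservation: the protocol's Cox list also includes other interventions received, which arises after randomisation and was not simulated.

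**Site is not excluded.** This also stands. The covariate list is given by example, so it would be wrong to read the protocol as leaving site out of every analysis. It is unnamed. Nor does the protocol say that site predicts walking; it calls site a potential confounder and reserves the prognostic claim for sitting balance.

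**Stratified allocation helps whatever the test.** Correct. Plain t-test power rises from 0.915 to 0.946 as R² goes from 0 to 0.3, so only part of the gain goes unclaimed. Gait quality is measured only in those who walk, so balance within strata is only partly kept there and the conservatism may be weaker than simulated.

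**A condensed article leaves such detail to the analysis plan.** This stands in part; a full plan may name the strata. But the section names each test, gives the censoring rule for the logrank test and lists Cox covariates. As stated, those methods do not follow the stated design.

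**Conclusion.** The point holds as one of efficiency and consistency. The logrank test and the two-group tests are stated without the factors used to randomise, and they are conservative if those factors are prognostic. At HR 2 the logrank test loses about 1 point of power at a sitting-balance ratio of 2, about 6 at 3 with a modest site effect, and about 11 to 14 at 4 with a site ratio of 2. Only in the last setting does power fall below the planned 80%. The t-tests lose about 1 to 3 points at 0.2 m/s and stay above 90%.

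All these sizes rest on assumed stratum effects. A reader might conclude that the actual type I error is below 5%; the documents cannot establish that, because they quantify no stratum effect, and with none there is no deficit. Nor is validity at risk: any error is on the conservative side, with no inflation of false positives.

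**What to change.** - **Time to walking:** either stratify the logrank test by sitting balance and site, or make a Cox model with treatment, sitting balance and site the main comparison. State which analysis is the main one.
- **Continuous gait and mobility outcomes:** compare the groups with linear models that include sitting balance and site. A van Elteren stratified rank test, where a rank test is used, is optional.

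Both factors are known at randomisation, so this needs only wording and no new data. If the strata turn out not to be prognostic, the six-stratum logrank test costs about 2 to 3 points of power (93.9% to 92.1% in step 3, 93% to 90% in step 4). Covariate adjustment costs essentially nothing (93% for the Cox model with or without site; 91.5% vs 91.6% for the t-test and the adjusted model).

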### Intervention

Both the experimental and the control group will undergo a maximum of 30 minutes per day of walking practice with assistance from one therapist, five days a week until they walk or until discharge from rehabilitation. The total daily time of intervention will be 30 minutes from beginning (ie, from when the participant is in the gym) to end (ie, when the participant is back in the wheelchair). This time therefore includes transferring, putting on aids or setting up equipment, ie, training does not have to be continuous so that rests may be taken. The amount of assistance during walking will be standardised to one therapist, however, additional help will be allowed during setting up walking (ie, getting the participant onto the treadmill for treadmill walking or into standing for overground walking). The rationale for this protocol is based on clinical observation of how much time and how many therapists are currently used in trying to get a non-ambulatory person to walk. Other intervention involving lower limb function, (ie, strengthening exercises, practice loading the affected leg during activities such as sitting, standing up and standing) will be standardised to 60 min per day. No other part of the multidisciplinary rehabilitation program will be controlled. Randomization should ensure that any effect of other interventions will be the same for both groups, therefore, other therapies will not be withheld.

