#### Control group

Training for the *control *group will involve current practice of assisted overground walking. If a participant is too disabled to walk with the help of one therapist, they will practise stepping forwards and backwards or standing with a knee splint and practising shifting weight from leg to leg. Aids such as knee splints, ankle-foot orthoses, parallel bars, forearm support frames and walking sticks can be utilised as part of training. Training aims to produce independent walking. Therefore, progression of training encompasses both increasing speed and reducing assistance from both aids and the therapist. Information describing the specific features of the training session (such as use of aids, distance walked, assistance required) will be recorded to monitor adherence to the guidelines and to be able to describe the intervention accurately.

The end-point of the training phase of the study will be either the attainment of independent walking or discharge from the rehabilitation unit. The end-point of the follow-up phase of the study will be 6 months after admission to the study.

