## Discussion

Australia, like many other developed nations, is undergoing a major demographic shift involving significant growth in the aged population. The Australian Government has recognised that a revolution is underway at the end of the life cycle. In its National Research Priorities, the Government has recognised that it will be important to promote healthy ageing and that this endeavour will be underpinned by research. Only by establishing evidence-based interventions, such as the one outlined in this project, will the severity of many health problems be reduced. In economic terms, if non-ambulatory patients do not learn to walk after their stroke, it is likely that they will require assisted care, placing a high burden on the community. Furthermore, given that independence in walking is a major factor in the decision to discharge patients from inpatient care, earlier independent walking should result in a reduction in length of hospital stay which should result in cost saving. The Queensland Health Report "Hospital benchmarking pricing model" has estimated the cost of a day in hospital for a neurological patient at $880. In summary, this study has the potential to reduce disability following stroke by improving the outcome of walking and thereby to reduce the burden of this condition on the community. Increasing the number of people who can walk after stroke should reduce the demand for nursing home placement.

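### The Cox comparison of the randomised groups adjusts for other interventions received, a post-randomisation variable, so its adjusted hazard ratio is liable to bias

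*Protocol article*

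**What the plan says.** The Statistical analysis section compares the proportion walking and the time to walking "using the logrank test, in which those who do not achieve independent walking are censored at the time they are discharged". It then adds a Cox regression to compare the times in the two groups "while allowing for possible confounding variables, such as other interventions received, and baseline sitting balance". It does not limit the first of these covariates to a pre-randomisation measure, make it time-dependent, or label the model exploratory. The same section does label the regression on lesion, neglect, spasticity and sensation as post-hoc.

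Other sections bear on that covariate:

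- **Intervention:** other lower-limb work "will be standardised to 60 min per day". Beyond that, "No other part of the multidisciplinary rehabilitation program will be controlled". The section adds that "Randomization should ensure that any effect of other interventions will be the same for both groups".
- **Control group (final paragraph):** "The end-point of the training phase of the study will be either the attainment of independent walking or discharge from the rehabilitation unit".
- **Discussion:** "independence in walking is a major factor in the decision to discharge patients from inpatient care".
- **Randomization:** "participants will be stratified according to Item 3 (Sitting Balance) of the Motor Assessment Scale for stroke", with site as the other stratification factor.

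**The concern.** A confounder of a group comparison must influence both group membership and outcome. Here group membership is set by randomisation, so nothing that happens later can confound it. What happens later can be a consequence of allocation, of the patient's progress, or of both. Adjusting for such a variable can remove part of the effect of allocation or create an apparent effect.

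The article itself supplies possible routes. Training stops at walking or discharge, and walking influences discharge. Any amount of therapy added up over the stay therefore grows with the time that is being analysed. Most of the programme is uncontrolled and therapists know the allocation, so the type or intensity of other therapy may also differ by group.

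At stake is the adjusted estimate for the second part of the main objective, whether walking is achieved earlier. This Cox model is the only model described that yields a hazard ratio, and the article gives no rule for reading it if it differs from the logrank result.

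**Working it through.** **1. The passages side by side.** The Intervention section says randomisation should equalise the effect of other therapies. If it does, they are not confounders and the reason given for adjusting falls away. If therapy differs by group after allocation, the difference may be a result of allocation, and adjusting for it changes the question. Neither case supports including it as a confounder.

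**2. The plan's own figure.** Inputs from the Sample size section: 50% v 75% walking at six weeks, two-sided 0.05, power 80%.

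- n = [1.96·√(2·0.625·0.375) + 0.8416·√(0.25 + 0.1875)]² / 0.25² = (1.342 + 0.557)² / 0.0625 ≈ 57.7, so 58 per group.
- With continuity correction: (57.7/4)·[1 + √(1 + 4/(57.7·0.25))]² ≈ 65.4, so 66 per group.

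The stated 65 per group is reproduced to within one patient. The point changes no stated figure.

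**3. The implied hazard ratio.** Under proportional hazards, 0.25 = 0.50^HR, so HR = ln 0.25 / ln 0.50 = 2.0. With 50% of controls walking at six weeks, the control median is 6 weeks.

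**4. Simulation at the trial's size.** 400 trials, 65 per arm, exponential times to walking, control median 6 weeks. The following are assumptions that are not in the article: independent discharge with median 16 weeks, and other therapy averaging 5 h/week (SD 1 or 2 h), unrelated to group. Ranges come from repeated runs.

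| Covariate added (true HR 2) | HR without → with | Power without → with |
|---|---|---|
| Total = weekly rate × observed time, SD 1 h | 2.01–2.04 → 1.34–1.40 | 93–96% → 31–37% |
| Same total, SD 2 h | about 2.0 → about 1.6 | about 90% → up to about 60% |
| Weekly rate unrelated to group and outcome | no material change | no material change |
| Weekly rate unrelated to group but prognostic (log HR 0.5 per SD) | 1.85 → 2.03–2.05 | 83–84% → 91–95% |

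With true HR 1, adjusting for the total (SD 1 h) left the estimate centred on 1 but rejected in about 10% of trials against a nominal 5%.

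**5. Second simulation, with an unmeasured severity factor.** 1,000 patients, 200 replicates, sitting balance always in the model. Its severity, discharge and therapy parameters are also assumptions. The baseline-adjusted estimate falls a little below 2 because severity is only partly captured.

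| Covariate added to sitting balance | True HR 2 | True HR 1 |
|---|---|---|
| Cumulative therapy to walking or discharge | 1.87 → 1.44 | 1.00 → 1.00 |
| Early intensity affected by group and sharing severity with the outcome | 1.88 → 2.07 | 1.00 → 1.09 |
| Unrelated to group and outcome | 1.89 → 1.89 | 1.00 → 1.00 |

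The upward shift in the middle row follows from the signs chosen: less therapy in the treadmill group, more in patients with a better outlook. Reversing one sign would reverse the shift.

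**The case against.** The strongest reply is that the article never says how the covariate is measured. The one amount it gives is a daily dose, which fits a rate at least as well as a total. The large attenuation comes only from a total, which places follow-up time inside its own model. If the covariate were a prognostic rate unaffected by group, adjustment would help, as the fourth row of the first table shows. The covariates are introduced as examples, and their exact form is commonly left to an analysis plan that is not shown. Because therapists know the allocation, looking for imbalance in other therapy is also a sensible supplementary aim.

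Much of this stands. It rules out saying that the adjusted estimate is biased by a known amount, or that the covariate can only be harmful or useless. It does not rescue the rule as written. A fuller plan could define the variable, but could not turn therapy received after allocation into a baseline confounder. The condition under which adjustment helps, independence from group, is one that the article hopes for but does not secure.

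A reader might also infer that any disagreement between the logrank and Cox results would be an artefact. The document does not support that: the Cox model also adjusts for sitting balance, a prognostic factor, and can properly differ from the logrank test for that reason alone.

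**Conclusion.** The concern holds in this form: the article names a post-randomisation variable as a confounder in a comparison of randomised groups, against its own reasoning in the Intervention section, and the adjusted hazard ratio is liable to bias. Size and direction are unknown because the measurement is not stated. For a cumulative total, a true hazard ratio of 2 would be estimated at about 1.3–1.6, with power of about 30–60% instead of about 90%. For an intensity affected by group and by severity, the shift can be upward, to about 1.09 under no effect. For a rate unrelated to both, there is none. These figures rest on assumed therapy and discharge distributions and are illustrations, not predictions for this trial.

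A reader might infer that the trial's main test is compromised. It is not: the unadjusted logrank test does not use this covariate, the sample size rests on an unadjusted difference in proportions, and nothing in the article makes the adjusted Cox estimate the deciding result. Adjustment for baseline sitting balance is sound.

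**What to change.** In the Statistical analysis section, restrict the Cox comparison to variables fixed before randomisation, namely the sitting-balance stratum and site, which are the two stratification factors. Remove other interventions received from that model. Report other interventions descriptively by group, which also checks whether the lower-limb standardisation was kept. If their role in walking outcome is of interest, examine it in a separate analysis labelled exploratory, stating how the variable is measured and over what period.

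The cost is about one sentence of text. It needs no new data, and the sample size stays at 130.

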### Participants

Stroke patients will be screened and invited to participate if they:

• are within 3 weeks of their first stroke

• are aged between 50 and 85 years of age

• are diagnosed clinically with hemiparesis or hemiplegia of acute onset, and

• are non-ambulatory defined as scoring 0 or 1 on the Motor Assessment Scale for stroke.

Participants will be excluded if they:

• have clinically evident brainstem signs

• have severe cognitive and/or language deficits which preclude them from following instructions in training sessions

• have unstable cardiac status which would preclude participation in a rehabilitation program, or

• have any pre-morbid history of orthopaedic conditions of the lower limbs which would preclude them from relearning to walk.

The presence of sensory loss, neglect and/or spasticity will not be exclusion criteria. However, their severity will be recorded using the Nottingham Sensory Assessment for sensory loss, the line bisection test for neglect, and the Ashworth Scale for spasticity. In addition, information about site and size of lesion will be collected.

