### Sample size

130 participants will be recruited. The sample size has been calculated to reliably detect a treatment effect size of a 25% increase in proportion of independent walkers with 80% power at a two-tailed significance level of 0.05. For non-ambulatory patients, it takes an average of 3 months to achieve independent walking with about 50% walking independently at six weeks [1]. We are interested in being able to detect a 25% increase, from 50% to 75%, proportion of non-ambulatory patients walking independently by six weeks. Only an effect such as this is clinically significant enough to warrant a change in the implementation of services which would involve the re-education of physiotherapists and the expense of purchasing a treadmill and overhead harness system. The smallest number of participants to detect this difference between two proportions estimated from independent samples is 65 participants per group, ie, 130 participants in total [23]. However, since the analysis of the data is survival curve analysis, there is greater power than the calculation would suggest because the effect of dropouts is minimal in this analysis. For example, in a pre-post design trial of 6 weeks intervention, if a subject dies or is lost to follow-up (ie, drops out) at 5 weeks, there is no measurement at the post-test on which to perform an analysis. In this trial, which ascertains once a week whether independent walking has been established, they would be censored at five weeks so that they no longer form part of the total sample. However, this participant's data would be available for the five weeks they participated in the trial thereby minimising the effect of their dropping out.

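### Time since stroke and age are known for every participant but named in no comparison, and the 6-month speed and 6-min distance tests take no baseline covariate: optional precision forgone, not an error

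*Protocol article*

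**What the plan says.** All references are to the protocol article.

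- **Participants.** Patients are eligible if they "are within 3 weeks of their first stroke" and "are aged between 50 and 85 years of age". Stroke date and age must therefore be established for everyone before randomisation.
- **Randomization.** Allocation is stratified by site and by sitting balance. Sitting balance is chosen because it predicts walking outcome.
- **Statistical analysis, time to walking.** The main comparison is an unadjusted logrank test, with non-walkers censored at discharge. A Cox regression follows, "allowing for possible confounding variables, such as other interventions received, and baseline sitting balance". Of its two examples, one is a baseline value and the other is recorded after randomisation.
- **Statistical analysis, 6-month outcomes.** The five walking-quality variables (including speed) and the four mobility variables (including 6-min distance) are compared by Student's t-test, or by Wilcoxon's rank-sum test if clearly not Normal.
- **Statistical analysis, post-hoc regression.** It uses lesion, neglect, spasticity and sensation. Age and time since stroke are absent.
- **Sample size.** The target is an increase "from 50% to 75%, proportion of non-ambulatory patients walking independently by six weeks", "with 80% power at a two-tailed significance level of 0.05". The number needed "is 65 participants per group, ie, 130 participants in total".
- **Control group (end-points).** "The end-point of the follow-up phase of the study will be 6 months after admission to the study".

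**The concern.** Follow-up is counted from admission to the study, but participants may be at different points after their stroke when they enter. With entry allowed over 3 weeks, two people seen six weeks after admission can be 6 and 9 weeks from their stroke. Ages can differ by 35 years. If either factor predicts walking, a comparison that ignores it is less precise than it could be.

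Both values are fixed before randomisation and already held, so adjusting for them introduces no bias and needs no new data. Only precision is at stake, and how much depends on how strongly the two factors predict the outcome.

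**Working it through.** **1. What each analysis allows**

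| Analysis | Covariates as written | Can age and time since stroke enter? |
|---|---|---|
| Logrank | none | no |
| Cox | open list of examples | yes, but not named |
| 6-month speed, 6-min distance | t-test or rank-sum | no; nor can sitting balance |
| Post-hoc regression | lesion, neglect, spasticity, sensation | not named |

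**2. The plan's own figure**

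Inputs from Sample size: 0.50 versus 0.75, two-sided 0.05, 80% power. The mean proportion is 0.625.

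n = [1.96·√(2·0.625·0.375) + 0.8416·√(0.25 + 0.1875)]² / 0.25² = (1.342 + 0.557)² / 0.0625 = 57.7, so 58 per group.

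With continuity correction: (57.7/4)·[1 + √(1 + 4/(57.7·0.25))]² = 65.4, so 66 after rounding up. The stated 65 reproduces to within one participant per group. Without the correction, 65 per group gives 84.6% power.

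On a time-to-event scale with exponential times, HR = ln 0.25 / ln 0.50 = 2.0. Expected walkers by six weeks are 65·0.50 + 65·0.75 = 81.25. Schoenfeld's formula needs 66 events, and 81 events give about 88% power.

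The 50% and 75% are group-wide rates. Any spread caused by age or entry time is already inside them, so the 65 per group is not affected.

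**3. What adjustment could add to the Cox comparison**

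The document gives no prognostic effect for either factor, so the strengths below are assumptions. Setting: 65 per arm, weekly tests to week 6, entry uniform over 3 weeks, and marginal six-week rates held at 50% and 75%.

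*Time since stroke only.* Power, unadjusted versus adjusted, from two separate simulations:

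| Rate ratio per week (log slope) | 700 replicates | 1,000 replicates |
|---|---|---|
| 1.0 (0) | not run | 87.0% vs 87.4% |
| 1.22 (0.2) | 88.7% vs 89.1% | 88.3% vs 89.5% |
| 1.35 (0.3) | 89.7% vs 90.9% | 88.5% vs 90.7% |
| 1.65 (0.5) | 88.4% vs 92.6% | 87.5% vs 90.9% |
| 2.23 (0.8) | 89.1% vs 97.3% | 89.5% vs 97.1% |

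Monte Carlo error is about 1 point per figure.

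*Time since stroke and age together.* At log-hazard slopes of 0.2 per week and per decade, power goes from about 85% to 87%. At 0.3 for both it goes from 87% to 92%. At zero there is no detectable loss.

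For scale, the hazard ratio across the full 3-week window is e^(3·0.3) = 2.5 at slope 0.3, e^(3·0.5) = 4.5 at 0.5 and e^(3·0.8) = 11 at 0.8. The last two rows are strong to extreme.

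*A less favourable setting.* Here the conditional HR is fixed at 2.0 and only the control rate is held at 50%. An unadjusted logrank test is compared with a Cox model adjusted for both factors (500 runs, error about 1.5 to 2 points). For HRs of 1.0, 0.8, 0.67 and 0.5 per week and per decade, power is 88% vs 85%, 87% vs 85%, 77% vs 78% and 63% vs 78%. Two features limit this version. The experimental rate drifts from 75% down to 68% across the four scenarios, and the two tests differ in more than the covariates. Type I error of the unadjusted logrank was 4% to 7%, consistent with 5%.

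**4. The 6-month outcomes**

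Adjustment multiplies the standard error of a mean difference by about √(1 − R²), where R² is the share of within-group variance that the covariates explain. For speed, Sample size gives SD 0.27 and 84 participants, so the unadjusted standard error is 0.27·√(2/42) = 0.059 m/s. If R² were 0.1 it would be 0.059·√0.9 = 0.056; if 0.2, 0.059·√0.8 = 0.053. These R² values only illustrate the formula; the document supports none of them.

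**The case against.** The best case for leaving the text alone has five parts.

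- **The Cox list is open.** It gives examples only, and a full covariate list is usually left to the full protocol or analysis plan. This stands. A reader might infer that the two factors stay out of the Cox model as noise, but the text does not say so. It does not answer the 6-month comparisons, where the named tests leave no room for a covariate.
- **The gain is assumed.** No prognostic strength is given, and below about 1.35 per week for time since stroke alone the gain is 1 to 2 points or less, within simulation error. This stands and limits the size of the point.
- **There is no shortfall.** With the 50% and 75% rates held, unadjusted power was 85% or more in every setting, above the planned 80%. The article already claims over 90% for walking speed. This also stands.
- **The 3-week spread is half the six-week horizon.** The arithmetic is right (3/6), but it is tempting to make too much of it. Three weeks is the permitted maximum, not the observed spread. Six weeks is the horizon used for sizing, while the analysis runs until walking or discharge. Against the 6-month end-point, 3 weeks is about 3/26 = 12%.
- **A larger adjusted hazard ratio is not a correction of bias.** At a rate ratio of 1.65 per week it moves from 2.02 to 2.14. That is the difference between a marginal and a conditional hazard ratio, and the unadjusted logrank test remains valid.

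**Conclusion.** The point holds as an optional improvement, not as an error or contradiction. Two baseline values held for everyone are named in no comparison, and 6-month speed and 6-min distance are tied to tests that also ignore the stratifier sitting balance.

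For the Cox comparison the likely gain runs from nothing to about 5 points of power at moderate assumed effects. It is larger (about 8 points at 2.23 per week) only at very strong ones. This rests on uniform entry over 3 weeks, exponential times, follow-up to week 6 and assumed prognostic slopes. For the 6-month outcomes no gain can be derived without an assumed R-squared.

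The document does not support reading this as bias, inflated type I error, loss of the planned 80% power or a fault in the 65 per group.

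**What to change.** In Statistical analysis:

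1. Pre-specify days from stroke to randomisation and age, together with baseline sitting balance, as baseline covariates in the Cox treatment comparison.
2. Compare 6-month walking speed and 6-min distance with a linear model adjusted for the same three baseline values. Keep the t-test or rank-sum test as a sensitivity analysis.

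The cost is wording only, since both added values are already established at screening. The two values use two degrees of freedom. The adjusted hazard ratio is conditional on the covariates and not directly comparable with the unadjusted one, so the report should label each. If a full protocol or analysis plan already names these covariates for the Cox model, only the second change remains.
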